### The intervention

The intervention that will be tested in this study, named Heuristic Method (HM), is a participatory action approach for diagnosis, development and implementation of workplace interventions [53]. HM has been developed and applied by a Dutch consulting firm in at least 100 public and private organizations in the last decade. The consulting firm refined the intervention after each application, based on the lessons learned. Although the customers were almost always satisfied with the intervention’s results, the intervention effects were never tested scientifically. The Heuristic Method is aimed at optimizing occupational self-efficacy and organizational efficacy. The purpose is to (1) use both management’s and worker’s knowledge, skills and perceptions to thoroughly determine what hinders and stimulates ‘healthy and happy working’ in the organization, so that (2) management and workers can develop their specific work-related action plan and implementation plan that ultimately will reduce need for recovery and increase vitality. The first part of this purpose is addressed in the first phase of the intervention, named ‘needs assessment’. The second part of this purpose is addressed in the second phase of the intervention, the ‘implementation plan’. The needs assessment phase comprises three iterative steps led by an HM-facilitator: (1) interviews; (2) digital questionnaire; (3) group sessions, resulting in a plan of action. The components of the implementation phase can differ according to the maturity of the organization in applying organizational change processes. The minimum variant is remote counseling of the management team by a facilitator, in implementing the plan of action. Details on the application of both phases and their consequent steps in this study are provided below.

#### Phase 1: Needs assessment

The needs assessment is conducted in the tradition of participatory action research (PAR) [39]. Therefore, a participatory group of employees is constituted, comprising employees, a representative from the Workers Council, a staff member, a management member, the HM-facilitator and the researcher (six to eleven members in total). Its members are selected by the management team (with the exception of the facilitator and the researcher), based on their perception of the member’s capacity for ‘pioneering’ in organizational change processes. The HM-facilitator is an expert in organizational change processes. If the intervention group is scattered among several school locations, this will be taken into account when composing the group. The participatory group is named ‘Engine of Development’ and becomes the project’s ambassador throughout the needs assessment. The Engine of Development decides in collaboration how often they meet, but at least six times – before, during and after the three needs assessment steps.

The intervention kicks off with an information session, held after baseline measurement, led by the HM-facilitator and facilitated by the management. In the information session the HM-facilitator outlines the steps of the upcoming intervention and the researcher presents several outcomes of the baseline measurement.

##### Step 1: In-depth interviews

The Engine of Development approaches some prominent colleagues for an in-depth, open interview with the HM-facilitator. Prominent colleagues can be the typical optimists, pessimists, innovators, integrators or otherwise interesting employees that help the HM-facilitator grasp both initial hindrances to happy and healthy working as well as implicit norms in the intervention group. Approximately ten interviews will be held, or until saturation is reached. The HM-facilitator writes a report on his findings that is sent to all employees, after consulting the Engine of Development and the management team, respectively.

##### Step 2: Digital, open ended questionnaire

Based on the report of the in-depth interviews, the Engine of Development compose the questions for a digital, open ended questionnaire. The open ended questionnaire should further specify the hindrances that were found in the in-depth interviews. All employees in the intervention group are invited to take part in the questionnaire. The HM-facilitator writes a report on the findings that is sent to all employees, after consulting the Engine of Development and the management team, respectively.

##### Step 3: Group sessions

Based on the report of the open ended questionnaire, the Engine of Development determines several clusters of hindrances that need to be specified further in group sessions. The aim of the group sessions is not only to specify hindrances, but also to propose work-oriented solutions. All employees in the intervention group are invited to take part in the group sessions, which are chaired by the Engine of Development (except for the researcher). To ensure ‘freedom of speech’, the management team and staff have their own group sessions.

##### Result: Plan of Action

The HM-facilitator adds his own observations, experiences and assessment of (un)healthy implicit norms in the intervention group to the compressed analyses of hindrances and solutions offered in the in-depth interviews, open questionnaire and group sessions. This results in a plan of action that supposedly reflects opinions, perspectives and (feasible) wishes of employees in the intervention group (i.e. management and workers). The plan of action is sent to all employees, after consulting the Engine of Development and the management team, respectively. If the work-oriented solutions proposed also concern higher management (i.e. Executive Board or Board of Directors), then the management team is advised to inform higher management on the findings as well.

#### Phase 2: Implementation

In the implementation phase of the participatory action approach, the management has to take the first step. With support of the Engine of Development, the management team decides on which work-oriented solutions will be implemented. The solutions can be either evidence-based (e.g. adjusting classroom schedules), or new, tailor-made and specific to the context (e.g. adjusting the physical layout of class rooms). In any case, the management team explains to the employees which work-oriented solutions are (not) implemented and to what end. Furthermore, the method prescribes that the management team equips the plan of action with an implementation plan comprising amongst others a timeframe, a budget and the allocation of roles (e.g. the Engine of Development’s role). If the management team wishes, the HM-facilitator will take up a role during the implementation phase, for example in monitoring the plan’s progress or coaching the management team.

### Primary and secondary outcomes

#### Measuring instruments: primary outcomes

##### Need for recovery

(Early) symptoms of fatigue at work are considered indicative of a ‘need for recovery’ [54]. Need for recovery after a working day is measured using a subscale of the Dutch Perception and Evaluation of Work Questionnaire (Dutch abbreviation: VBBA) [54]. The questionnaire comprises 11 dichotomous (*yes/no*) items and has proven to be valid and reliable (alpha 0.86) [54].

##### **Vitality**

Vital workers show high levels of energy and mental resilience, persist when facing difficulties and are willing to invest effort in their work [50]. Vitality is measured using the vigor subscale (3 items) of the Utrecht Work Engagement Scale-9 [55]. Responses are to be given on a seven point scale (0 = *never* to 6 = *always/every day*). The vigor subscale has shown acceptable validity and reliability in a sample across ten countries [50].

#### Measuring instruments: secondary outcomes

##### Job demands and resources

Several aspects of the job and its content are measured using subscales of the Dutch version of the Job Content Questionnaire (JCQ) [56]: psychological demands, coworker and supervisor support and decision authority. The psychological demand dimension measures the mental work load, organizational constraints on task completion and conflicting demands (5 items) [56]. The coworker and supervisor support subscales measure socio-emotional as well as instrumental support (8 items) [56]. Four identically phrased, but explorative items were added on socio-emotional and instrumental support of (higher) management. Decision authority or autonomy measures the workers’ possibilities to make decisions about their work, mediated by organization factors (3 items) [56]. Response scales range from 1 = *strongly disagree* to 4 = *strongly agree.* The subscales of Dutch JCQ used in this study have shown acceptable scale reliability and validity [56].

Furthermore, possibilities for professional growth are assessed by a 6-item subscale of a Dutch questionnaire, developed for the (primary) educational sector (in Dutch: Welzijnscheck Onderwijspersoneel) [57], which has shown good divergent validity and reliability (alpha 0.87) [58]. Response scales range from 1 = *strongly disagree* to 5 = *strongly agree.*

##### Work ability

Work ability is based on the workers’ balance between resources and demands and determines job performance now and in the near future [59]. Work ability is measured using the Work Ability Index (WAI) [60]. The WAI is a self-report instrument and comprises seven dimensions on the physical and mental demands of work and the health and resources of the employee. For the current study, two of the seven dimensions were deemed relevant: 1) perceived current work ability, compared to lifetime best (1 item) and 2) perceived work ability related to mental job demands and perceived work ability related to physical job demands (2 items). Responses on (1) are recorded on a frequency scale from 0 (*unable to work*) to 10 (*very good)*. Responses on (2) are recorded on a five-point frequency scale from 1 (*very good*) to 5 (*very bad*). Reliability and validity have been shown to be adequate in a Dutch sample (alpha 0.63 to 0.71) [61].

##### Job satisfaction

Job satisfaction is operationalized as workers’ satisfaction with the job and its conditions. Job satisfaction is measured by two items of the Netherlands Working Conditions Survey 2010 [62]: to what extent are you, all things considered, satisfied with (1) your job, and (2) your working conditions? Response scales range from 1 = *very dissatisfied* to 5 = *very satisfied*.

##### Commitment

It has been shown that teacher commitment is a predictor of burnout, sickness absence and retention [63]. Therefore, commitment to work (2 items) and the organization (3 items) is measured in this study, using the Dutch questionnaire NOVA-WEBA [64,65], which has shown moderate validity and reliability (alpha 0.68) [66]. Response scales range from 1 = *strongly disagree* to 5 = *strongly agree*.

##### Work engagement

Work engagement is defined as a positive, fulfilling, work-related state of mind that is characterized by vigor, dedication and absorption [55]. The Utrecht Work Engagement Scale (UWES) [55] is the most commonly used instrument to measure work engagement [67]. The 9-item version of UWES is used in this study, response scales range from 0 = *never* to 6 = *always/every day*. UWES-9 has shown good validity and reliability [68].

##### Health

Health is measured by asking a single item of the free version of SF-36-v2, named RAND-36 [69]. This single item measures perceived general health (“How do you rate your health in general?”) on a five-point frequency-scale from 1 = *bad* to 5 = *excellent*. The subscale is considered valid and reliable (alpha 0.81) [69].

##### Sickness absence

Sickness absence is considered working less than normal hours or days due to illness, an incident or any other health reason. Sickness absence data will be collected in two ways: from company records as well as at baseline and follow-up measurements.

At baseline and follow-up, presence, frequency and duration of sickness absence in the past 12 months is measured by three items from the Netherlands Working Conditions Survey 2010 [62]. Furthermore, the self-reported cause of the last case of sickness absence is measured and whether this cause was attributed (fully, partly or not) to the work (NWCS 2011) [3].

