## Methods/Design

A quasi-experimental field study is conducted to determine the effectiveness of the participatory action approach (phase 1: needs assessment) and tailored work-oriented solutions (phase 2: implementation plan), compared to business as usual. The study is designed as a controlled trial (CT) with mixed methods (quantitative and qualitative) and three measurement moments: T0 at baseline (quantitative measurement), T1 at six months (quantitative and qualitative measurement) and T2 at 18 months (quantitative and qualitative measurement) (Figure 2). A CT is necessary to control for random changes, although the researchers are well aware of the fact that they are conducting a *social* experiment and that causal relations are thus embedded in complex contexts [38]. Randomization to experimental group (intervention group) or control group is practically impossible in this project, as often in organizational level workplace interventions [38], due to the aspirations of participating schools. Both schools participate in the study because they aim to solve a problem or reach a goal within a specific department of the school. The experimental groups were thus selected by the schools. To reduce the negative impact of selection bias, the control groups are selected by the researchers according to the ‘general control’ matching principle (or: frequency distribution control) [48]. Matching criteria are: department size (at least 150 employees), mean age of employees, and type of work (i.e. teaching vocational students and not secondary school pupils). Since the assignment to groups was out of our control, we will examine in the analyses whether propensity score matching is necessary. By applying the statistical technique of propensity score matching, the effect of the intervention can be estimated accounted for covariates that predict receiving the intervention. This way we expect to nullify potential confounding bias [49].

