#### Sample size

The sample size calculation is based on the number of cases required to detect a small (Cohen’s d = 0.2) effect on the primary outcome vitality, as measured with the 3-item subscale of the 9-item version of the Utrecht Work Engagement Scale (UWES-9) [50]. The baseline mean vitality score (range 0–6) is assumed to be 4.01 (SD = 1.14), based on the scores of 9,679 Dutch and Belgian employees [51]. A 5% increase of the mean score on vitality in the intervention group after 12 months is considered relevant and feasible (4.21; SD 1.20).

The required sample size is then 385 (193 for both intervention and control group; thus 97 per intervention and control group per school), assuming a significance level (α) of 0.05, two-sided tests and power (1-β) of 0.80 [52]. A non-response and loss to follow-up of 35% is taken into account, so that a total sample size of 600 is needed.

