### Data analysis

#### Effect evaluation

The effectiveness of the intervention on primary outcomes (need for recovery and vitality) and secondary outcomes at short term (T1), long term (T2) and corrected for baseline values, will be established by multilevel analyses. Repeated measurements on the worker-level and clustering of observations can thus be taken into account. The data will be analyzed at three levels: 1) worker, 2) department, and 3) school. Both crude and adjusted linear and logistic regression analyses will be conducted. The intention-to-treat principle is leading in all statistical analyses, meaning that the analyses are based on the initial treatment assignment and not on the treatment eventually received. However, per-protocol analysis will also be conducted, restricting the comparison to the ideal participants, in this study: participants that report taking part in at least two of the three steps of the needs assessment.

Multilevel analyses wherein T1 functions as the dependent variable, will be adjusted for possible confounding factors (e.g. experience, overtime). These variables will also be checked for effect modification at all measurement moments.

For all analyses, a two-tailed significance level of p < 0.05 will be considered statistically significant. The multilevel analyses will be conducted by means of MlwiN 2.0; linear and logistic regression analyses will be performed using SPSS 17.0 (SPSS Inc. Chicago, Illinois, USA).

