#### Information provision on measurement

Prior to baseline measurement employees in the intervention and control group will receive verbal and written information on the baseline measurement. Employees in the intervention group will be informed verbally by the participatory group (Engine of Development) by presentations at team meetings. Employees in the control group will be informed by their immediate supervisors during team meetings. Management in both the inter2vention and control group will be informed by the facilitator during a management meeting. All groups will receive a digital letter with information about the baseline measurement.

Furthermore, the agenda of a team meeting will be cleared, to enable employees to fill out the questionnaire(s) during this time frame.

All employees and managers participating in the baseline measurement are requested to sign an informed consent at the start of the questionnaire. By signing the informed consent participants declare amongst other things: 1) to have received information on the baseline measurement and the study, 2) to understand they can withdraw at any time from the study without reason. A similar procedure will be applied for the first follow-up (T1, 6 months) and second follow-up (T2, 18 months).

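### Self-reported sickness absence is asked over 12 months at the 6-month follow-up, so half of that window precedes the intervention and was already counted at baseline

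*Protocol article*

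**What the plan says.** The Sickness absence section under the secondary outcomes fixes the recall period: "At baseline and follow-up, presence, frequency and duration of sickness absence in the past 12 months is measured by three items". No different period is given for the first follow-up. The same section names a second source: "Sickness absence data will be collected in two ways: from company records as well as at baseline and follow-up measurements". It states no period for the company records.

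Methods/Design sets the timing: "T0 at baseline (quantitative measurement), T1 at six months (quantitative and qualitative measurement) and T2 at 18 months". The section on information provision on measurement confirms that both later waves are follow-ups: "A similar procedure will be applied for the first follow-up (T1, 6 months) and second follow-up (T2, 18 months".

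Phase 1: Needs assessment places the start of the intervention: "The intervention kicks off with an information session, held after baseline measurement".

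Effect evaluation plans a short-term test for these outcomes: "secondary outcomes at short term (T1), long term (T2) and corrected for baseline values, will be established by multilevel analyses".

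**The concern.** A 12-month recall question put six months after baseline reaches back six months before it. Those months cannot carry an intervention effect. They also lie inside the period reported at T0, so the T1 outcome and the baseline value used to correct it share the same absences.

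What is at stake is the short-term reading of one secondary outcome. A real early reduction would look smaller in relative terms than it is. The same item at T2 covers only time after baseline, so part of any growth in the relative effect from T1 to T2 could come from the change in window and be credited to the implementation phase.

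**Working it through.** The article gives no absence rate, effect size or power for sickness absence, so there is no stated figure to reproduce. The windows follow from the text. The sizes rest on labelled assumptions.

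**Inputs from the article.** Recall W = 12 months (Sickness absence). Waves at 0, 6 and 18 months (Methods/Design). Intervention starts after T0 (Phase 1). T1 effect corrected for baseline (Effect evaluation).

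**Step 1: windows.** For follow-up at month F, the post-baseline share is min(F, W)/W and the overlap with the T0 window is max(0, W - F)/W.

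| Wave | Months covered | Post-baseline share | Overlap with T0 window |
|---|---|---|---|
| T0 | -12 to 0 | 0 | n/a |
| T1 | -6 to +6 | 6/12 = 50% | 6/12 = 50% |
| T2 | +6 to +18 | 12/12 = 100% | 0% |

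**Step 2: relative effect on frequency and duration.** Assume a constant absence rate, alike in both groups before T0, and a constant rate ratio RR from T0. Then observed RR at T1 = 0.5 + 0.5 × RR.

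- RR 0.90: 0.5 + 0.45 = 0.95, so 10% appears as 5%
- RR 0.80: 0.5 + 0.40 = 0.90, so 20% appears as 10%
- RR 0.70: 0.5 + 0.35 = 0.85, so 30% appears as 15%

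On the log scale, 49%, 47% and 46% of the effect is kept. If the effect starts 1, 2 or 3 months after T0, the affected share of the window is 5/12 = 42%, 4/12 = 33% or 3/12 = 25%.

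**Step 3: presence (yes/no).** Assume Poisson onset, so risk = 1 - exp(-rate × time). With an assumed 12-month prevalence of 50% and RR 0.80, the risk difference is 0.0743 for a fully exposed 12-month window and 0.0359 for the T1 window: 0.0359/0.0743 = 48%. Over assumed prevalences of 30 to 70% and RR 0.7 to 0.8, the kept share is 46 to 49%.

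**Step 4: precision on the absolute scale.** For days or spells, the pre-baseline half adds the same expected amount to both groups, so the expected difference equals that of a 0-6 month item. The variance does not. Let A, B and C be absence in months -12 to -6, -6 to 0 and 0 to +6, each with variance 1 and common correlation r. The baseline value is A + B. After linear adjustment for it:

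- 12-month item at T1 (B + C): 2 + 2r - (1 + 3r)²/(2 + 2r)
- 6-month item at T1 (C): 1 - (2r)²/(2 + 2r)

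| r | B + C | C | Ratio |
|---|---|---|---|
| 0 | 1.500 | 1.000 | 1.50 |
| 0.3 | 1.212 | 0.862 | 1.41 |
| 0.5 | 0.917 | 0.667 | 1.38 |
| 0.7 | 0.574 | 0.424 | 1.35 |

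For the same power on the same absolute difference, the 12-month item therefore needs about 1.35 to 1.5 times the participants.

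**The case against.** The case for leaving the plan alone has several parts.

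- **Limited reach.** Sickness absence is one of many unranked secondary outcomes, no sample size rests on it, and the problem touches one source at one wave. This stands. A reader might take absence to be the trial's main organisational outcome. The article does not say so. It names absence only as an example of an organisational outcome.
- **Only the relative scale is halved.** This stands for days and spells. A reader might infer that the T1 effect is biased by half on every scale. Step 4 shows that for counts and days the cost is precision.
- **Baseline correction helps.** A reader might infer that the required sample doubles. That figure holds only without adjustment and with uncorrelated half-years (variance 2 against 1). The article plans to correct for baseline, which removes part of the shared noise and leaves 1.35 to 1.5. Adjustment does not restore the relative effect.
- **T1 and T2 answer different questions by design.** True: T1 concerns the needs assessment, T2 also the implemented solutions. But a change of exposed share from 50% to 100% is an artefact on top of that intended difference.
- **Company records are planned.** They could supply a clean T1 measure, and a condensed article may leave the extraction period to the full protocol. This makes the remedy cheap. It does not change the stated self-report window or the stated T1 test of that outcome.
- **The wording comes from a national survey.** Keeping it has value, and at T0 and T2 it can be kept.

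**Conclusion.** The point holds, within limits. The T1 self-report items mix six months before baseline with six months after it, and the first six are also in the T0 answer. That follows directly from the stated recall period and timing and needs no assumption.

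The sizes do need assumptions. The relative reduction in frequency or duration at T1 appears as half its true size if the absence rate is constant and the effect begins at T0. This is the favourable case, because the needs assessment itself takes place after baseline. The absolute difference is unchanged if the groups are alike before T0, with residual variance 1.35 to 1.5 times that of a 0-6 month item for equal-variance half-years with correlation 0 to 0.7. The reductions of 10, 20 and 30% are illustrations; the article gives none.

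The documents do not support reading this as a flaw in the sickness absence evaluation as a whole. The T2 window is clean, the records can be cut to the right period, and need for recovery and vitality are not involved.

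**What to change.** For the T1 effect on sickness absence, do one or both of the following:

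1. Take T1 absence from the company records, limited to T0-T1, with the pre-baseline record period as baseline covariate. This needs only a date filter, provided the records are obtained per employee and reach back before T0.
2. Ask the T1 self-report items about the past six months, anchored to the baseline questionnaire. Analyse frequency and duration per month (T0 value/12, T1 value/6). Analyse presence as a 6-month yes/no outcome adjusted for T0 presence, because a monthly rate does not suit a yes/no item.

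Keep the 12-month items at T0 and T2. With a 6-month item at T1, the two follow-ups then cover months 0 to 18 once, without gap or overlap.

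If the T1 wording cannot be changed, state that the T1 self-report item is not interpreted as a short-term effect, and rely on the records.

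The cost is small: one changed time reference or one date filter. The downside of the second option is that the T1 item departs from the national survey wording and has a different recall length from T0, so the two are not strictly the same measure.
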